#### Pilot Study

##### Overview

The pilot study will be a prospective one-year assessment of the implementation of a package of combination HIV prevention services. In addition to providing information on acceptability and uptake of the prevention package, the longitudinal study will develop capacity for conducting prospective data collection and providing prevention interventions and services. Data from the pilot study will also allow for refinement of estimates of key model parameters and support development of training curricula.

Approximately 200 MSM, 100 each in Cape Town and Port Elizabeth, will be followed for a period of 12 months. Participants will be offered prevention interventions, including condom choices with an assortment of styles, sizes, and features; condom-compatible lubricant choices, including water- and silicone-based types; couples HIV testing and counseling (CHTC) [14,15]; and PrEP for eligible men. Non-occupational post-exposure prophylaxis (nPEP) for men with an exposure at high risk for HIV transmission will be made available. Data on service utilization, condom use, HIV and STI incidence, acceptability of the prevention package, HIV-related knowledge, and other outcomes will be collected.

##### Participants and Enrollment

Men eligible to participate in the study will be aged 18 years and older, self-report anal intercourse with a man in the past year, be current residents of the study city, plan to stay in the city for the next year, be able to answer survey questions in English, Xhosa, or Afrikaans, be male sex at birth, be willing to provide contact information, and have a phone to facilitate the scheduling of study clinic visits. All study participants will provide written informed consent prior to participating in the pilot study.

The study will enroll both MSM who are living with HIV (HIV-positive) and those who are HIV-negative. Up to 20% of men followed for one year will be living with HIV. Additional HIV-positive men recruited will be enrolled for a baseline visit only and will not count towards the 100 men per site sample size. Recruitment and enrollment will be monitored in stages to ensure sufficient HIV-negative men are enrolled to adequately assess elements of the HIV prevention package. Enrollment of HIV-positive men will be monitored in steps. Once five HIV-positive men are enrolled prospectively at baseline, prospective enrollment of positives will pause until 20 HIV-negative men are enrolled. Men who seroconvert during follow-up will remain in the study for the full follow-up period. Recruitment activities will be conducted for approximately 3 months or until 100 MSM have been recruited and enrolled in each city. In both Cape Town and Port Elizabeth, MSM will be recruited from multiple areas including urban areas, peri-urban communities, and township areas in order to recruit diverse communities of MSM. We will employ different methods of recruitment, including event- and venue-based, online, participant referral, and walk-ins at study clinics. Men who meet the eligibility criteria during recruitment will be asked to provide contact information and be scheduled for an enrollment baseline visit.

##### Study Design and Procedures

Men will be screened at recruitment, and eligible men will be invited to attend a baseline enrollment visit. Following consent and enrollment, the baseline visit will include a self-administered behavioral survey, HIV prevention counseling and testing, and a clinical exam (Figure 3). The clinical exam will assess STI history, circumcision status, STI and liver disease symptoms, and include laboratory testing for syphilis, urethral and rectal chlamydia and gonorrhea, hepatitis B, and urine drug screening. HIV-negative men will have additional testing for creatinine, liver enzymes (aspartate transaminase–aspartate aminotransferase/alanine transaminase–alanine aminotransferase [AST/ALT]), serum phosphate, proteinuria, and glycosuria to assess eligibility for PrEP. A dried blood spot specimen card will be prepared and stored. Men who present with STI symptoms will be prescribed medication at the visit. Participants can receive referrals for HIV treatment and care, circumcision, STI treatment (if outside the scope of study-provided treatment), alcohol and drug abuse counseling, and domestic violence counseling as needed. Men who test positive for STIs at baseline will return to the study clinic for treatment (if not prescribed medication during the visit). Men who are hepatitis B susceptible will be offered to initiate the hepatitis B vaccination series at their next study visit.

Follow-up study visits at 3, 6, and 12 months will include surveys, HIV prevention counseling, HIV testing for men who tested HIV-negative at their last visit, a clinical exam assessing STI symptoms, and blood and urine collection. At the 6-month and 12-month visits, all men will be tested for syphilis, and urethral and rectal chlamydia and gonorrhea. Men on PrEP will have additional monitoring at their standard and PrEP study visits and additional PrEP visits 1 month after initiating PrEP, and at 9 months to assess creatinine level, AST/ALT levels, phosphorus, proteinuria, glycosuria, HIV testing, medication adherence, and to monitor side effects. Men who test positive for HIV will have blood drawn for CD4 and HIV viral load testing. Prospectively enrolled HIV-positive participants will have additional CD4 testing at 6 and 12 months and HIV viral load testing at 3, 6, and 12 months.

**Figure 3 figure3:**
[figure not shown]
Visit schedules by participant type.

##### Study Intervention

The intervention package will be available starting at baseline and continuing throughout the study and will include condom and condom-compatible lubricant choices, risk reduction counseling, CHTC, linkage to care for HIV-positive men, and PrEP with emtricitabine/tenofovir disoproxil fumarate for eligible men for initiation at a 1-month or 4-month visit (Figure 4).

At their baseline visit, all participants will receive a package with condom and condom-compatible lubricant choices: ribbed, colored, flavored, fitted, thin, and flared condoms, and silicone-based and water-based lubricants. Participants will be given a Condom Scorecard to rate their condom preferences, to be returned at their next study visit (Multimedia Appendix 7). At all follow-up study visits, participants will be encouraged to pick up their preferred condom and lubricant types. Participants can also drop in to each study clinic during study clinic hours to pick up additional condoms and condom-compatible lubricant.

HIV testing will be provided to all men at their baseline visit. Risk-reduction counseling will be provided to all men regardless of their HIV status and at all standard and PrEP visits. Risk reduction counseling will be client-centered, according to the Centers for Disease Control and Prevention’s (CDC) Fundamentals of HIV Prevention Counseling curriculum. HIV testing will be provided to all men at their 3, 6, and 12-month visit who tested negative at their previous visit. HIV testing will be performed by counselors trained in using South African provincial HIV testing protocols.

Participants will be invited to schedule CHTC appointments with a clinic counselor at any point after they complete their baseline visit. The CHTC model differs from individual testing in that a couple receives HIV testing and counseling at the level of the couple, with tailored messaging based on dyadic characteristics. Participants can attend multiple CHTC sessions with different partners; these partners do not have to be enrolled in the study to participate. All CHTC sessions will be performed by counselors who completed a 3-day training curriculum on CHTC for MSM.

Men who test positive for HIV at baseline or during the study will be linked to HIV treatment and care services as needed, including antiretroviral medication and mental health services. Referrals will be made to local providers known to be MSM-friendly.

PrEP will be available for men who meet the following eligibility criteria: HIV-negative, high-risk for acquiring HIV, adequate kidney and liver functioning, initiated hepatitis B vaccine series if susceptible, not known to have hypertension or diabetes, and willing to follow PrEP dosing and visit guidelines [16]. Men who express interest and meet eligibility criteria at their baseline visit can initiate PrEP at a 1-month initiation visit. For men who do not initiate PrEP at 1 month and later express interest and meet the eligibility criteria, PrEP will be available to initiate at a 4-month initiation visit. PrEP visits will follow the guidelines determined by the Southern African HIV Clinicians Society [16]. Throughout the study, as part of the standard of care, nPEP for men with an exposure at high risk for HIV transmission will be available.

Community-level interventions include community mobilization efforts to improve health literacy and uptake of prevention services among MSM, and training of health care providers and clinic and study staff to deliver sexual health services to MSM. Community mobilization efforts began in 2012 to build the necessary capacity to conduct the pilot study, to obtain feedback on the study protocol (eg, this feedback informed our decision to include HIV positive men), and to identify and establish appropriate and accessible clinic sites in Port Elizabeth. Community leaders and members of community organizations were consulted to determine how to include HIV prevention and health education messages as part of study recruitment events. Through engagement with the community, community members have been considered and hired in study staff positions and therefore are able to play a key role in the collection, presentation, and validation of data that characterize this population. We plan to engage with the community throughout the pilot study to further create community ownership over the interventions and facilitate uptake of the interventions. The previously mentioned provider trainings will ensure that MSM in the community have access to health care from MSM-friendly clinics and providers trained in MSM-specific health issues, improving the quality of care available to MSM in the community.

**Figure 4 figure4:**
[figure not shown]
Intervention components.

##### Data Collection

Data will be collected via case report forms, self-administered surveys during study visits, and monthly short message service (SMS) surveys. Paper-based case report forms will be used to capture eligibility and enrollment data, as well as all clinical assessments, interventions, laboratory results, adverse events, and social harms reporting (Multimedia Appendix 8). All case report forms will be completed by study staff, rather than participants. These forms will be sent by scan to Emory University, with data captured using DataFax, and securely stored in participant study binders at the DTHF and HSRC offices.

At each standard study visit, participants will complete surveys on iPads or computers via SurveyGizmo, which has secure servers and a Health Insurance Portability and Accountability Act business partner agreement with Emory. Surveys will be offered in English, Xhosa, and Afrikaans (Multimedia Appendix 9). Surveys were translated from English to Xhosa and Afrikaans, then back-translated to ensure conceptual and cultural equivalence. These surveys will collect data on demographics, current use of health care services, history of HIV and STI testing, outness to health care providers, alcohol and substance abuse, history of sexual activities and condom and condom-compatible lubricant use, barriers to safer sex practices, stigma, knowledge of HIV transmission and prevention strategies, and the participant’s sexual network.

An SMS survey will be sent to consenting participants each month. These brief surveys will collect information on recent sexual activity with male and female partners, including the number of partners, frequency of sex acts, condom use, lubricant use, and HIV testing outside of the study.

##### Outcomes

Study outcomes will be a combination of process-level outcomes, prevention impact outcomes, and acceptability and knowledge, attitudes and behaviors data, outlined in Figure 5.

**Figure 5 figure5:**
[figure not shown]
Study outcomes.

##### Data Analysis Plan

The primary design for analysis will be a pre-post design. For measures that are collected from MSM participants (eg, use of condom and condom-compatible lubricant, disclosure of male sex partners to providers), data will be compared between baseline surveys and follow-up surveys. Bivariate analyses will be conducted by comparing proportions of men reporting a behavior between baseline and follow-up, using chi-square statistics. If differential retention results in follow-up data being available from a group with substantially different characteristics (eg, if older men are differentially retained, so that the 12-month participants are considerably older than the baseline sample), stratified analyses or regression modeling may be used to account for potential confounders. For biological measures, we will describe the prevalence of HIV, syphilis, chlamydia, and gonorrhea at baseline and will calculate the incidence of HIV, syphilis, chlamydia, and gonorrhea during prospective follow-up. We will conduct an intent-to-treat analysis; participants who are lost or withdraw from the study will be considered failures in analysis of uptake of the particular intervention or service of interest. HIV-positive participants who are enrolled for a baseline visit only will be included in analyses to understand prevalent behaviors and clinical features, like HIV viral load, access to care, and condom use.

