##### Sample Size

Our pilot feasibility study is not powered to measure differences in pre-post measures in clinical outcomes; rather, we hope to develop reasonable estimates of the prevalence of certain behaviors at baseline and of the incidence of HIV infection and STIs, which may be important endpoints in a larger, future prevention trial. The choice of 100 participants per site is based on feasibility within time and budgetary constraints and will provide reasonable estimates of key parameters, including retention in the cohort and uptake of PrEP.

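### The chi-square comparison of baseline with follow-up names no paired method although the same men are measured at both times; read as an independent-samples test, it is conservative and may miss real behavior change

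*Protocol article*

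**What the plan says.** The pilot study is a single cohort without a control group. Its Overview says: "Approximately 200 MSM, 100 each in Cape Town and Port Elizabeth, will be followed for a period of 12 months". Study Design and Procedures places surveys at baseline and at 3, 6 and 12 months.

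The Data Analysis Plan opens with "The primary design for analysis will be a pre-post design" and gives condom and lubricant use and disclosure to providers as examples of the measures compared. It then names its one test: "Bivariate analyses will be conducted by comparing proportions of men reporting a behavior between baseline and follow-up, using chi-square statistics".

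The sentence after that deals with differential retention. Its example is the case "if older men are differentially retained, so that the 12-month participants are considerably older than the baseline sample", and its remedy is that "stratified analyses or regression modeling may be used to account for potential confounders". No paired test, GEE or mixed model is named in the article.

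Two other statements bear on the point. The Data Analysis Plan says "HIV-positive participants who are enrolled for a baseline visit only will be included in analyses to understand prevalent behaviors and clinical features". The Sample Size section says "Our pilot feasibility study is not powered to measure differences in pre-post measures in clinical outcomes" and bases 100 men per site on feasibility.

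**The concern.** The Pearson chi-square test for two proportions treats the baseline and follow-up answers as coming from different people. Here they come from the same men. Habits such as condom use tend to persist within a man, so the two answers are likely to be positively correlated. The variance of the change is then smaller than the test assumes.

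The consequence would be p-values that are too large, and intervals that are too wide if they are built on the same variance. A real shift in behavior could be reported as no clear change. The Discussion says the pilot results will feed into the final package and the design of the larger trial, so the precision attached to behavior change matters even in a pilot.

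**Working it through.** **Is there a figure to reproduce?** No. The article gives no alpha, prevalence, effect size, within-man correlation or retention for this comparison, and the sample size rests on feasibility.

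**Paired or unpaired?** McNemar's statistic is also referred to a chi-square distribution, so the word alone does not settle it. Three features favor the two-sample reading:
- The text compares proportions at two times, not change within men.
- The retention sentence sets the 12-month participants against the whole baseline sample.
- That sentence treats age as a confounder. In a paired contrast each man is his own control, so a difference in age between the full baseline sample and the retained men cannot confound it, although selective retention can still limit whom the result describes.

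**Inputs.** From the article: n = 200, the same men at both times. Assumed: two-sided alpha 0.05; p1 = p2 = 0.50 under no change, or 0.50 rising to 0.60; within-man correlation ρ from 0 to 0.7; full retention at first.

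**Formulas** (q = 1 − p):
- SE assumed by the unpaired test = √[(p1q1 + p2q2)/n]
- True SE on the same men = √[(p1q1 + p2q2 − 2ρ√(p1q1p2q2))/n]

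With p1 = p2 = 0.50 and n = 200, the unpaired SE is √(0.50/200) = 0.0500 and the true SE is 0.0500 × √(1 − ρ). The ratio is 1/√(1 − ρ), and the true type I error is 2[1 − Φ(1.96/√(1 − ρ))].

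| ρ | Unpaired SE | True SE | Ratio | Type I error, unpaired |
|---|---|---|---|---|
| 0 | 0.0500 | 0.0500 | 1.00 | 5.0% |
| 0.2 | 0.0500 | 0.0447 | 1.12 | 2.8% |
| 0.3 | 0.0500 | 0.0418 | 1.20 | 1.9% |
| 0.5 | 0.0500 | 0.0354 | 1.41 | 0.6% |
| 0.7 | 0.0500 | 0.0274 | 1.83 | 0.03% |

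The share of information given up is 1 − 1/ratio², which equals ρ: none at 0, 20% at 0.2, 50% at 0.5 and 70% at 0.7.

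**Power for 50% to 60%.** Worked at ρ = 0.5:
- The true SE is √[(0.25 + 0.24 − 2 × 0.5 × √0.06)/200] = 0.0350.
- The unpaired test needs a difference above 1.96 × √(2 × 0.55 × 0.45/200) = 0.0975. Power is Φ[(0.10 − 0.0975)/0.0350], about 0.53.
- McNemar's test, with 25.5% of men discordant, needs 1.96 × √(0.255/200) = 0.0700. Power is Φ[(0.10 − 0.0700)/0.0350], about 0.80.

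Across ρ = 0, 0.2, 0.3, 0.5 and 0.7, McNemar's power is 0.52, 0.61, 0.67, 0.80 and 0.95. The unpaired test stays at 0.52 to 0.54.

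**Simulation check** (40,000 replicates, ρ = 0, 0.3, 0.5, 0.7). The unpaired type I error was 0.052, 0.021, 0.006 and 0.0003. McNemar's stayed at 0.051 to 0.053, with power 0.52, 0.67, 0.81 and 0.97.

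**Incomplete follow-up.** With an assumed 80% retained at random, the unpaired test uses 200 baseline and 160 follow-up answers, and McNemar uses 160 pairs. Simulated power was 0.48, 0.47, 0.47 and 0.46 unpaired, against 0.44, 0.57, 0.72 and 0.93 for McNemar. At zero correlation McNemar is slightly worse, because it drops men without a follow-up survey. A model over all visits addresses that.

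**The case against.** The best defense has four parts.

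**The article never says the test is unpaired.** This is true. A reader might infer that the plan commits to an independent-samples test, but the text leaves pairing unspecified. The two-sample reading is a strong inference from ordinary usage and the retention sentence. A condensed article may leave details to a statistical analysis plan. Here, however, it names the test itself, and the name in its usual sense does not fit the design.

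**The size is assumed.** This also stands. A reader might conclude that most of the precision is thrown away. The article gives no correlation, and at zero correlation nothing is lost. The loss is large only at moderate to high correlation, and a change well above 10 points may be found by either test.

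**The error is conservative.** This stands for positive correlation. A reader might fear false claims of benefit, but type I error falls below 5% and the estimated proportions do not change.

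**The pilot claims no power.** This stands in part. The Sample Size section disclaims power for clinical outcomes, and its stated estimation aims do not depend on this test. But the Data Analysis Plan makes pre-post the primary analysis design and applies the chi-square comparison to behaviors. Limited power does not justify a standard error that ignores the design.

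**Conclusion.** The point holds as a moderate one. The only named test for the pre-post comparison of behaviors specifies no pairing, and on its most natural reading it treats one cohort as two independent samples. Standard errors and p-values for change are then wrong at any non-zero within-man correlation, and too large when the correlation is positive. Over assumed correlations of 0.2 to 0.7 the standard error is overstated by 12% to 83%.

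This rests on the two-sample reading and on a positive correlation, which is plausible but not given. It does not make the pilot invalid: baseline prevalence, HIV and STI incidence, retention and PrEP uptake are estimated as before. Nor does the article say that the baseline-only HIV-positive men enter the pre-post test. It places them in analyses of prevalent behaviors and clinical features, and an explicit exclusion would remove any doubt.

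**What to change.** Replace the chi-square sentence with wording such as:

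> Change in each behavior from baseline will be estimated within participants, as a paired risk difference with 95% confidence interval and McNemar's test among men with both surveys, or by a GEE or mixed logistic model over visits, clustered on participant, which also uses men with incomplete follow-up. HIV-positive men enrolled for a baseline visit only do not enter this comparison.

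One of the two approaches should be chosen before the data are examined. McNemar's test is simpler but drops men without a follow-up survey. The model keeps them, at the price of an assumption about why surveys are missing.

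The cost is a few lines of analysis text, with no new data and no change in sample size. Each man's survey records must be linked across visits. The cohort design implies this, since follow-up HIV testing already depends on each man's previous result, but the article does not spell it out for the survey data.

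### The primary pre-post comparison appears to set retained men against the wider baseline sample, and correction for attrition is optional, so selective retention can appear as behaviour change in either direction

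*Protocol article*

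**What the plan says.** The Data Analysis Plan states: "The primary design for analysis will be a pre-post design". For what participants report, such as condom and lubricant use, the method is "comparing proportions of men reporting a behavior between baseline and follow-up, using chi-square statistics". It mentions neither a paired test nor a restriction to men seen at both times.

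The attrition rule begins with a condition: "If differential retention results in follow-up data being available from a group with substantially different characteristics". The example is that older men stay more often, "so that the 12-month participants are considerably older than the baseline sample". In that event "stratified analyses or regression modeling may be used to account for potential confounders". No threshold is given for how different the groups must be.

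A separate rule deals with men who leave: "participants who are lost or withdraw from the study will be considered failures in analysis of uptake of the particular intervention or service of interest". It covers uptake, not the pre-post behaviour measures.

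The same section adds: "HIV-positive participants who are enrolled for a baseline visit only will be included in analyses to understand prevalent behaviors and clinical features". The Pilot Study overview gives the cohort size: "Approximately 200 MSM, 100 each in Cape Town and Port Elizabeth, will be followed for a period of 12 months".

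**The concern.** Age at enrolment cannot confound a comparison of the same men at two times, because it is identical on both sides. It can do so only if the two sides hold different men. The plan's own example therefore implies that retained men are compared with a wider baseline group.

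A change in who is observed can then be reported as a change in what men do. The safeguard is weak in three ways: it depends on a judgement made once the data are in, it is permissive, and it is illustrated by a demographic trait, whereas retention linked to the behaviour itself does more damage.

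The pilot has no control arm in which selective loss might cancel. The stigma section also hypothesises that services will reduce stigma, and the Conclusions and Discussion carry the pilot's results into the design of a larger trial.

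**Working it through.** **The plan's own figures.** The article states no retention rate, effect size or error rate for this comparison, so there is nothing to reproduce beyond the counts. These agree: 2 × 100 = 200 men, of whom up to 20% (40) are HIV-positive, leaving 160 HIV-negative.

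**Assumed inputs.** p is baseline prevalence of the behaviour; r1 and r0 are retention in men with and without it at baseline; ρ is the within-man correlation between baseline and follow-up. True prevalence does not change.

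**Step 1: stable behaviour (ρ = 1).** Follow-up prevalence among retained men is q = p·r1 / [p·r1 + (1 − p)·r0].

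With p = 0.50, r1 = 0.90, r0 = 0.70: q = 0.45 / (0.45 + 0.35) = 0.45 / 0.80 = 0.5625. Against the full baseline of 0.50 this is +6.3 points, with no man changing. If the two retention rates are swapped, q = 0.35 / 0.80 = 0.4375, or −6.3 points.

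**Step 2: behaviour that varies within men.** Retained men show p + ρ(q − p) at follow-up. The bias is therefore ρ(q − p) against the full baseline, and −(1 − ρ)(q − p) against the same retained men's own baseline.

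With ρ = 0.5 and 90%/70% retention, a man with the behaviour at baseline has it again with probability 0.75, and a man without it has it later with probability 0.25. Follow-up is 0.5625 × 0.75 + 0.4375 × 0.25 = 0.531.
- Against the full baseline: 0.531 − 0.500 = +3.1 points.
- Complete pairs: 0.531 − 0.5625 = −3.1 points, which is regression to the mean.

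**Step 3: range at p = 0.50, in percentage points.**

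| Retention with / without the behaviour | Full baseline, ρ = 1 | Full baseline, ρ = 0.5 | Complete pairs, ρ = 0.5 |
|---|---|---|---|
| 85% / 75% | +3.1 | +1.6 | −1.6 |
| 90% / 70% | +6.3 | +3.1 | −3.1 |
| 95% / 65% | +9.4 | +4.7 | −4.7 |
| 85% / 50% | +13.0 | +6.5 | −6.5 |

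At p = 0.30 and ρ = 1 the same four pairs give +2.7, +5.5, +8.5 and +12.2.

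**Step 4: selection on age alone.** Suppose half the men are older, the behaviour is at 60% in older and 40% in younger men, and retention is 90% and 70%. Follow-up is (0.45 × 0.60 + 0.35 × 0.40) / 0.80 = 0.5125, or about +1.3 points. The trait used as the plan's example does less harm than retention tied to the behaviour.

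**Step 5: the test.** In 20,000 simulated cohorts of 200 men with p = 0.50 and no true change, the ordinary chi-square test at the 5% level rejected in 0.0%, 1.3%, 28.6% and 80.6% of runs for the four retention pairs at ρ = 1. With equal 80% retention and ρ = 0.5 it rejected about 1% of the time, against about 5% for McNemar's test. It is therefore conservative when there is no selection, and strong selection can still overwhelm it.

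**Step 6: weighting.** In the 90%/70%, ρ = 0.5 case, weight retained men by 1/0.90 or 1/0.70. The numerator is 0.45 × 0.75/0.90 + 0.35 × 0.25/0.70 = 0.375 + 0.125 = 0.50, and the denominator is 0.50 + 0.50 = 1. Follow-up prevalence is 0.50 and the bias is zero.

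**The case against.** The best defence has four parts.

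- **The text never says that unmatched men are compared, and chi-square statistics need not exclude McNemar's test.** This stands in part: the full-baseline comparator is an inference. It is a strong one, because the age example has no force under a same-men comparison.
- **Differential retention is named, remedies are named, and age is only an example, so baseline behaviour could also trigger adjustment. Finer detail belongs in a full protocol or SAP.** Model details can indeed wait. But the article itself fixes the contrast, the type of test and a conditional, permissive trigger; that is a choice, not a gap.
- **This is a feasibility pilot, and the Sample Size section disclaims power for pre-post differences in clinical outcomes.** True, but low power does not excuse bias in estimates meant to inform a larger trial. Uptake is protected by counting lost men as failures; behaviour measures are not.
- **The bias may be small.** This stands: under modest selection it is a few points and seldom significant.

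Two stronger readings lack support. A reader might infer that the bias flatters the package because safer men stay; the document gives no basis for a direction. A reader might also infer that baseline-only HIV-positive men inflate or dilute the pre-post baseline. The plan assigns them to describing prevalent behaviours, and Participants and Enrollment keeps them outside the 100 per site. Nothing places them in the pre-post contrast; their exclusion is simply not spelled out.

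**Conclusion.** The point holds as a weakness in the primary analysis: an apparently unmatched comparison, with an attrition correction that is optional and judged after the event. Selective retention can appear as behaviour change; the document does not show that it will, or in which direction.

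In the central illustration the bias is +6 points with fully stable behaviour and about +3 at within-man correlation 0.5. Across the retention patterns tried at 50% prevalence it runs from about 1.6 to 13 points. All of this rests on assumed prevalence, retention and correlation, since retention is something the pilot is meant to estimate.

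It would also be wrong to conclude that restricting to complete pairs settles the matter. At correlation 0.5 that replaces +3.1 with −3.1.

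**What to change.** - Make the pre-post analysis a within-man repeated-measures model (GEE or mixed) using all visits of all prospectively enrolled men. Use inverse-probability-of-retention weights, or equivalent conditioning, based on baseline age, site, HIV status and the baseline value of the behaviour.
- Run it regardless of observed imbalance. A GEE needs the weights: without them, under working independence, it would return the same unmatched contrast.
- Report the complete-pairs (McNemar) comparison as a sensitivity analysis only.
- State that baseline-only HIV-positive men serve to describe baseline prevalence and do not enter pre-post comparisons.

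Surveys at baseline and at 3, 6 and 12 months already supply the data, so no new participants or measurements are needed. The cost is a few sentences, modest extra programming and slightly wider intervals from weighting. One limit remains: the weights remove selection explained by the baseline variables, not loss driven by behaviour that changes after the last observation.
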